### Statistical analysis

2.6

SPSS for windows 24.0 statistical analysis software will be used for calculation, and normality test and homogeneity test of variance will be performed on each group of data. For measurement data in which the data conforms to the normal distribution, we will use the mean ± standard deviation. For non-normally distributed measurement data, the median ± quartile interval is used. General data comparison between the 2 groups using independent sample *t* test. Comparisons before and after treatment will be performed using *t* test for paired data. One-way analysis of variance will be used for comparison between groups. X^2^ test will be used for count data, and nonparametric rank sum test will be used for rank data. All statistical tests are two-sided. *P* < .05 indicates a significant difference.

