**Methods/design::**

We will select 60 patients diagnosed with SA. They will be randomly divided into intervention group and control groups. The control group will be given conventional treatment measures. The intervention group will receive acupuncture. Efficacy will be evaluated by comparing the skin lesion score and dermatological quality of life index before and after treatment.

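### Efficacy is worded and tested partly as within-arm before/after change, no test is named as decisive, and the between-arm ANOVA, though valid, names no baseline covariate

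*Protocol article*

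**What the plan says.** The Methods/design paragraph of the abstract says: "Efficacy will be evaluated by comparing the skin lesion score and dermatological quality of life index before and after treatment". That sentence names no contrast between the arms, although it follows the description of two randomised groups.

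Section 2.6 (Statistical analysis) lists these tests for measurement data:
- "General data comparison between the 2 groups using independent sample *t* test", apparently meant for baseline characteristics.
- "Comparisons before and after treatment will be performed using *t* test for paired data".
- "One-way analysis of variance will be used for comparison between groups". No covariate is named, and neither is the dependent variable (post-treatment score, change or percentage change).

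For other data types the chi-square "test will be used for count data, and nonparametric rank sum test will be used for rank data". On significance: "All statistical tests are two-sided", and P "< .05 indicates a significant difference". No test is singled out as the one on which the efficacy conclusion rests.

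Section 2.4.1 uses the baseline in one place. The efficacy index is the percentage reduction from the pre-treatment score, and response categories are added into a total effective rate.

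**The concern.** A paired t test in the acupuncture arm asks whether that arm changed, not whether it changed more than control. Both arms receive the hair-washing care and the rehabilitation education (sections 2.3.1 to 2.3.3), so both may improve for reasons unrelated to acupuncture. The abstract makes before/after the efficacy criterion, section 2.6 attaches a 5% test to it, and nothing makes the between-arm result decisive. The plan therefore does not rule out reading significance in one arm only as a treatment effect.

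The second matter is smaller. With two groups, one-way ANOVA is the independent-sample t test (F = t²). It makes no covariate adjustment for a pre-treatment score that the trial collects anyway. In a 60-patient trial the lost precision is worth having.

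**Working it through.** **The plan's own figure.** Section 2.5 gives 60 patients, 30 per arm. No effect size, SD, power or dropout is stated, so 60 cannot be reproduced. For orientation, at two-sided 5% the normal approximation gives 80% power at (1.96 + 0.84) × √(2/30) ≈ 0.72 SD, and 49% power at 0.5 SD.

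**Inputs from the protocol.** 30 per arm; two-sided 5% for each test; paired t within arm; one-way ANOVA between arms.

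**Assumed inputs, not in the protocol.** Baseline–post correlation r of 0.3, 0.5 or 0.7; equal SD before and after treatment; a common true change in both arms (no acupuncture effect).

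**1. Significance in the acupuncture arm only.** The arms are independent. If each paired test has power p, then P(acupuncture arm only) = p(1 − p):
- p = 0.3: 0.3 × 0.7 = 21%
- p = 0.5: 0.5 × 0.5 = 25%, the maximum
- p = 0.8: 0.8 × 0.2 = 16%

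A valid two-sided 5% between-arm test favours acupuncture wrongly in 2.5%.

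A simulation of 100,000 trials with r = 0.5 and a common change of 0.37 SD gave 50.2% significance in the acupuncture arm. It gave 25.1% for acupuncture only and 50.0% for exactly one arm. The between-arm t test on the post score held its level at 4.9%.

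The figure depends on the common change. Using noncentral t power with 29 df, P(acupuncture arm only) is:

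| Common change (SD) | r = 0.3 | r = 0.5 | r = 0.7 |
|---|---|---|---|
| 0 | 4.8% | 4.8% | 4.8% |
| 0.2 | 12.4% | 15.1% | 20.0% |
| 0.3 | 19.7% | 22.9% | 24.9% |
| 0.4 | 24.5% | 24.6% | 17.1% |
| 0.5 | 23.8% | 18.6% | 6.7% |
| 0.8 | 5.0% | 1.1% | 0.0% |

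These paired tests are two-sided, so the zero-change row counts both directions. With a large common change the one-arm-only pattern becomes rare, because both arms are then nearly always significant. The paired tests still say nothing about acupuncture against control.

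**2. Precision of the between-arm comparison.** Relative variance of the treatment difference: post score 1; change score 2(1 − r); ANCOVA 1 − r². The ANCOVA saving is r² against the post score. Against the change score it is 1 − (1 − r²)/[2(1 − r)] = (1 − r)/2.

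| r | Post | Change | ANCOVA | Saving vs post | Saving vs change |
|---|---|---|---|---|---|
| 0.3 | 1 | 1.40 | 0.91 | 9% | 35% |
| 0.5 | 1 | 1.00 | 0.75 | 25% | 25% |
| 0.7 | 1 | 0.60 | 0.51 | 49% | 15% |

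For an assumed true difference of 0.73 SD with 30 per arm, power is 80.7% for the post score at every r. For the change score it is 66.6%, 80.7% and 95.4%. For ANCOVA it is 84.2%, 90.4% and 97.7%. At 80% power ANCOVA would need about 27, 23 and 16 per arm, against 30 for the post score.

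**The case against.** The strongest reply is that a valid between-arm test is planned and that the abstract sentence may be loose wording for comparing the groups on pre- and post-treatment scores. Section 2.6 does provide that test, and its type I error is about 5%. What remains is that the abstract does not say so, the paired tests carry the same significance threshold, and no sentence ranks one above the other.

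Four stronger readings are tempting, and the document does not support them:
- *A result significant in one arm only is meant to count as evidence.* No sentence says this. The 25% is the error rate of an inference the plan leaves open, not of a stated decision rule.
- *The baseline is ignored.* The efficacy index in section 2.4.1 is a percentage change from baseline, and the ANOVA's dependent variable is unnamed, so it could be a change score. What can be said is that no baseline covariate is named. This is why the saving is given against both alternatives. At r = 0.7, for example, the gain over a change score is modest (97.7% against 95.4% power).
- *Paired t and ANOVA are the only efficacy tests.* Chi-square and rank sum tests are listed too and would compare the effective rate and the grades between the arms.
- *Skewed scores are still tested by ANOVA.* Section 2.6 plans normality and variance checks and a different summary for non-normal data. It does not say which test follows, and the four-level indicators could be treated as rank data.

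It is also fair to say that covariate adjustment is often left to an analysis plan. Here, however, a specific unadjusted method is stated, and a better one is available from data already collected.

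**Conclusion.** The point holds in limited form. Efficacy is described as before/after change and tested by within-arm paired t tests at 5%, beside a valid but unadjusted between-arm ANOVA, and none of these is named as decisive. If within-arm significance were read as a treatment effect, a trial with no acupuncture effect could show it in the acupuncture arm alone in up to about 25% of cases (16% to 21% at 80% or 30% power per paired test), against 2.5% for the between-arm test. These figures assume equal true change in both arms. The lack of baseline adjustment affects precision only. Its size depends on a correlation the protocol does not give and on which score the ANOVA takes: 9% to 49% of variance against a post score, 35% to 15% against a change score, as r goes from 0.3 to 0.7. ANCOVA has the smallest variance at every r shown.

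**What to change.** - In section 2.6, state that the between-arm difference in the symptom score decides efficacy on the continuous score.
- Analyse it by ANCOVA of the post-treatment score on treatment and baseline score, and report the adjusted mean difference with its 95% CI. Do the same for the DLQI.
- Keep the total effective rate with its chi-square or rank sum comparison as planned.
- Report paired before/after changes in each arm as description only, without drawing efficacy conclusions from their P values.
- Reword the abstract so that efficacy is evaluated by comparing the two groups.

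The cost is small. Section 2.8 says recruitment has not started, no new data are needed, and the named SPSS software fits ANCOVA. The downsides are slightly more analysis work and one added model assumption, a linear effect of baseline. The authors must also commit to the post-treatment score as the dependent variable for the continuous analysis, which the present text leaves open.

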### Data management

2.7

Information obtained from the evaluation of each participant will be recorded on a paper print-out. The information will then be handwritten on a paper document case report form and entered into an Excel file for future statistical analyses. In accordance with the Personal Information Protection Act, the names of all participants will not be disclosed, and a unique identifier number given during the trial will be used to identify participants. All of the participants will be informed that the clinical data obtained in the trial will be stored in a computer and will be handled with confidentiality. The participants’ written consent will be stored by the principal investigator.

### Ethics

2.8

The study protocol is going to be approved by the ethics committee of the Huabei Petroleum General Hospital. The study will be conducted under the Declaration of Helsinki principles, as well as following the norms of good clinical practice. Recruitment of patients has not started in this study. The study plan will be submitted to the ethics committee of the Huabei Petroleum General Hospital for review. We will not start recruiting participants without the consent of the ethics committee. The protocol of this study has been registered in the Chinese Clinical Trial Registry with the number ChiCTR2000030430.

## Discussion

3

Modern research has shown that cerebral cortical function is mapped to corresponding parts of the scalp.^[9,10]^ Acupuncture stimulates the function of the cerebral cortex to locate the corresponding scalp area, improves brain electrical activity, and increases the alpha wave index voltage. The alpha wave can relax one's spirit, thereby achieving the effect of regulating emotions.^[11]^ Other studies have shown that acupuncture of the head can cause changes in cerebral blood flow. Hemorheology showed a marked improvement in cell aggregation and a decrease in blood viscosity.^[12]^ The cerebral blood flow chart shows that the average amplitude is high, the inflow time is shortened, and the changes in left and right cerebral blood flow tend to be balanced.^[13]^ Therefore, acupuncture can relax blood vessels, improve blood vessel elasticity, and increase cerebral blood flow. Modern medical research has found that SA is related to the accumulation of dihydrotestosterone in the hair follicle.^[14]^ Acupuncture on the head can regulate the local blood flow of the head, can antagonize the accumulation of dihydrotestosterone, and achieve the effect of treating SA.^[15]^ In addition, SA brings stress to patients and may produce negative emotions such as anxiety and depression. Acupuncture on the head improves brain electrical activity and enhanced alpha waves can relax one's spirit and avoid a series of negative effects such as anxiety and depression.

An important feature of hair growth is its periodicity. The reason is that the growth of hair follicles is periodic.^[16]^ The existence of hair follicles is a prerequisite to ensure hair growth and replacement. The growth cycle is divided into 3 phases: growing phase, degenerative phase and resting phase. About 90% to 95% of normal hair follicles are in the growth phase, 1% enter the degenerative phase, and 5% to 10% are the resting phase.^[17,18]^ When the resting phase is reached, the hair falls off, and the hair follicles enter the next growth cycle. The duration of the growth phase determines the length of the hair. The first long-term occurrence is about 2 to 6 years, the regression period is 2 to 3 weeks, and the rest period is 2 to 3 months.^[19]^ The proportion of hair follicles during growth and resting determines the degree of hair thinning. When the growth period is shortened and the number of hair follicles is increased during the resting phase, clinical signs of exfoliation occur.^[20]^ There are many clinical studies on SA, but the overall study design is not rigorous. Some clinical reports did not establish a control group or did not follow random and blind methods. Efficacy evaluations in most studies are highly subjective. Such as hair growth, itching degree, amount of dandruff, etc, lack of objective quantitative standards, evaluation standards are not unified and objective. Therefore, we will use a standardized clinical randomized controlled research method to evaluate the efficacy of acupuncture treatment of SA. The intervention group and the control group were treated 3 times a week, with 4 weeks as a course of treatment and a total of 3 courses of treatment. This is beneficial to reducing the effect of the hair rest cycle on the experimental results. We hope to provide a higher level of evidence for acupuncture treatment of SA, while also providing patients with more treatment options.
